### Periodontal measures

The same study dentist will be performing all the periodontal examinations. Periodontal clinical parameters used to make the periodontal diagnosis are ‘plaque index’ (PI), ‘bleeding on probing (BOP)’, ‘periodontal pocket depth (PPD)’ and ‘clinical attachment loss (CAL)’ and will be measured at baseline (gestational week 11–20), and at gestational week 35–36 in the intervention group. PI will be measured during treatment (up to four treatment sessions before gestational week 35).

PI will be calculated as the mean of the amount of dental plaque present on each tooth. BOP will be calculated as the mean gingival bleeding observed 10 seconds after probing and will be recorded as a percentage. CAL will be measured (in ‘mm’) as the distance from the cemento-enamel junction to the base of the gingival sulcus [30]. PPD will be measured (in mm) as the distance from the gingival margin to the base of the gingival sulcus [30].

As per the clinical definition of periodontitis, a patient will be diagnosed with periodontitis, if a CAL of at least 1 mm is observed on at least two non-adjacent teeth, or a facial/ lingual CAL of at least 3mm is observed on at least two teeth (which may be adjacent) [31]. The observed CAL must not be due to reasons other than periodontitis e.g., traumatic gingival recessions, cervical dental caries, endodontic lesion draining through the marginal periodontium, vertical root fracture or complications associated with the second molar [31]. Periodontitis will further be classified into stages as per the severity of the disease, defined by the worst affected tooth with the highest observed CAL. Due to the lack of radiological diagnosis, CAL, PPD and number of missing teeth, will be the diagnostic criteria for staging periodontitis: StageⅠ(CAL = 1–2 mm, PPD ≤ 4 mm, no missing teeth), StageⅡ (CAL = 3–4 mm, PPD ≤ 5 mm, no missing teeth), Stage Ⅲ (CAL ≥ 5 mm, PPD ≥ 6 mm, 1–4 missing teeth) and Stage Ⅳ (CAL ≥ 5 mm, PPD ≥ 6 mm, ≥ 5 missing teeth) [31].

### Blood samples

The recruited women will have blood samples collected at either Holbaek or Nykoebing Falster Hospital at the Department of Clinical Biochemistry. Centrifuged and isolated plasma will be stored in Region Zealand Biobank for later analyses. Analyses of the blood samples will be done at Copenhagen Center for Translational Research at the Capital Region of Denmark. Blood will be taken at three time points, at baseline in gestational week 11–13 (from all recruited participants, n = 1200) and in gestational week 20–22 and at gestational week 35–37 from the included women (n = 600).

Inflammatory markers interleukin (IL)- 1β, IL-6, IL-10, IL-17α, (hs-CRP) and tumour necrosis factor (TNF)-α, hormones (insulin, leptin, growth differentiation factor (GDF)-15, adiponectin, resistin) and glycemic markers haemoglobin A1c (HbA1c) will be measured, and the blood samples will be analyzed in one batch at the end of the study to minimize variation. CRP and HbA1c will be measured and analysed on the same day the samples are taken. Saliva samples will be collected at baseline in gestational week 11–13 from all recruited participants and again at gestational week 35–37 from the included women. Procedures are the same for all women in both the intervention and the control group.

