**Methods and analysis:**

The PROBE study is a non-randomized controlled intervention study conducted among 600 pregnant women with periodontitis. The women will be recruited among all pregnant women at two Danish hospitals in Region Zealand during their nuchal translucency scan and will subsequently be screened for periodontitis. The intervention group includes 300 pregnant women, who will be offered state-of-the-art periodontal treatment during pregnancy. The control group includes additional 300 pregnant women, who will be offered periodontal treatment after giving birth. Outcome measures include periodontal measures, inflammatory, hormonal and glycaemic markers as well as the prevalence of preterm birth risk, low birth weight and risk markers of gestational diabetes mellitus (GDM) and preeclampsia that will be collected from all screened women and further during pregnancy week 20 and pregnancy week 35 for women enrolled in the intervention.

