## Materials and methods

### Design

Approval was granted by the Committees on Health Research Ethics in the Capital Region of Denmark (journal number H-20083249) on May 19, 2021 and by the Danish Data Protection Agency. The study will be conducted in accordance with the Helsinki Declaration and guidelines for Good Clinical Practice. The study was registered on clinicaltrials.gov (NCT06110143). The PROBE study is a controlled intervention study, where approximately 1200 pregnant women are recruited from Holbaek Hospital and Nykoebing Falster Hospital in Region Zealand in Denmark. About half of the participants are expected to have periodontitis, based on findings from other Nordic countries (1). The recruitment will take place in relation to their appointment for the nuchal translucency scan in gestational week 11–14 followed by a periodontal screening visit with a licensed dentist. The secretaries orally inform all pregnant women attending the nuchal translucency scan about the study. The pregnant women who participate will give informed written consent. Inclusion criteria for the intervention are pregnant women, who speak and understand Danish and are scheduled to give birth and either Holbaek Hospital or Nykoebing Falster Hospital, and are diagnosed with periodontitis (stage I-III) by the study dentist. Exclusion criteria are pregnant women without periodontitis, pregnant women with less than 20 healthy teeth, pregnant women with periodontitis who receives periodontal treatment and pregnant women with periodontitis stage IV.

Data from the Danish Dental Association (2019) indicate that approximately 35% of Danish women (18–39 years) with regular dentist visits have periodontitis. In the same age group, an estimated 65% of the women living in Region Zealand have regular dentist visits. There is no information about periodontitis for those 35%, who do not visit a dentist regularly. Recruitment of pregnant women with periodontitis into the study will last over a period of 18 months for the intervention group and an additional 18 months for the control group. Over a period of 18 month, we expect that approximately 600 pregnant women in the region are eligible for inclusion. Provided half of the invited women accepts the invitation to participate we can include 300 women in each of the two study arms.

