### Analyses of blood samples

Blood will be drawn by venipuncture into 2 ml EDTA tubes. The blood will be mixed by inversion and centrifuged at 900g in 15 min. The supernatant will be isolated, aliquoted, and stored at −80°C until analysis. Plasma levels of the proinflammatory cytokine IL-1β, IL-6, IL-10, IL-17α, TNF-α will be measured in duplicate by operators and blinded to the clinical state of the participant using Meso Scale Discovery (MSD; Rockville, MD) according to the manufacturer’s instruction. S-Plex, cat# 151B3S-1 (IL-6), cat# 151C3S-1 (IL-17α), cat# K151E3S-1 (TNF-α) and cat# K151Y2S-1 (IL-10). Analysis will be conducted on the MSD QuickPlex SQ 120 with software and the biomarker absolute values reported as absolute concentrations in picogram per milliliter (pg/ml).

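### With sequential arms and one end-of-study assay, intervention plasma is stored about 18 months longer at each visit, and the main-effect fallback exposes stored markers to any storage loss

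*Protocol article*

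**What the plan says.** The abstract describes the design: "The PROBE study is a non-randomized controlled intervention study conducted among 600 pregnant women with periodontitis". Under Design, recruitment "will last over a period of 18 months for the intervention group and an additional 18 months for the control group". The same section expects about 600 eligible women per 18 months and adds: "Provided half of the invited women accepts the invitation to participate we can include 300 women in each of the two study arms". Since half of 600 is 300, each arm fills one 18-month period, and I read the two periods as consecutive, with intervention first.

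Under Blood samples, plasma is drawn at gestational weeks 11–13, 20–22 and 35–37, and "the blood samples will be analyzed in one batch at the end of the study to minimize variation". Two markers are exempt: "CRP and HbA1c will be measured and analysed on the same day the samples are taken". That leaves ten stored markers: IL-1β, IL-6, IL-10, IL-17α, TNF-α, insulin, leptin, GDF-15, adiponectin and resistin. The section also says that procedures do not differ between the arms.

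Under Analyses of blood samples, "The supernatant will be isolated, aliquoted, and stored at −80°C until analysis", with "the biomarker absolute values reported as absolute concentrations in picogram per milliliter (pg/ml").

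Under Statistics, the adjustment set is age, BMI, parity, smoking, medicine use, socioeconomic status and education. The markers are analysed for change and by repeated measures ANOVA with group, time and group-time terms. If the interaction is not significant, it is removed and the main effects are tested.

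**The concern.** When one arm is recruited after the other and everything is assayed on one date, the earlier arm's plasma is older at assay. If a marker declines in the freezer, the intervention arm would show lower levels even if treatment did nothing. Assaying in one batch controls run-to-run variation, but it cannot undo a difference in age between the samples. Storage time is not among the covariates. Adding it would help little, because at a given visit the two arms share almost no storage times.

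Change in systemic inflammation is half of the stated aim, and knowledge of mediating inflammatory markers is a promised output. A lower concentration of IL-1β, IL-6, IL-17α or TNF-α in the intervention arm would read as benefit. For IL-10 or adiponectin a lower concentration would usually read as the opposite, so the bias could confuse the pattern across markers as well as flatter it.

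**Working it through.** **The plan's own figures.** The article gives no storage or marker calculation. Its Table 1 reproduces with a two-sided normal approximation, MDE = SD × (1.960 + 0.842) × √(2/n per arm):
- Gestational length: 2.06 and 2.52 days (stated 2.1 and 2.5).
- Birth weight: 129.7 and 158.9 g (stated 130 and 159).

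I use the same approximation below.

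**Storage time.** From the article: 18 months per arm, and visits near weeks 12, 21 and 36. Assumed: uniform enrolment, and assay when the last week-36 sample is drawn. That is month 36 + (36 − 12)/4.345 = 41.5. Mean enrolment is month 9 (intervention) and month 27 (control).

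| Visit | Intervention, mean months stored | Control, mean months stored | Gap |
|---|---|---|---|
| Baseline | 41.5 − 9 = 32.5 | 41.5 − 27 = 14.5 | 18.0 |
| Week 21 | 30.5 | 12.5 | 18.0 |
| Week 36 | 27.0 | 9.0 | 18.0 |

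A later assay date adds the same amount to both columns and leaves the gap unchanged. At baseline the ranges are 23.5–41.5 and 5.5–23.5 months, meeting only at the boundary. The ordering holds visit by visit, not across visits: about 5.5/18 = 31% of intervention week-36 samples are drawn after control recruitment begins.

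**Effect on levels.** Assume proportional loss r per year (no rate is in the documents). The intervention/control ratio with no treatment effect is (1 − r)^1.5 and the log shift is δ = −1.5 × ln(1 − r). With 300 per arm and an assumed log-scale SD of 0.5, the standard error is 0.5 × √(2/300) = 0.0408. The false-positive rate of a single-visit group comparison is 1 − Φ(1.96 − δ/SE) + Φ(−1.96 − δ/SE).

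| r per year | Ratio | δ | False-positive rate |
|---|---|---|---|
| 0 | 1.000 | 0 | 5.0% |
| 1% | 0.985 | 0.015 | 6.6% |
| 2% | 0.970 | 0.030 | 11.5% |
| 5% | 0.926 | 0.077 | 47% |
| 10% | 0.854 | 0.158 | 97% |

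The result depends on the SD: at 2% per year it runs from 7.5% (SD 0.8) to 24% (SD 0.3). With 200 per arm, 5% per year and SD 0.5, it is 34%.

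**Effect on change.** In both arms a woman's baseline sample is stored about 5.5 months longer than her week-36 sample. On the log scale, constant proportional loss therefore shifts every woman's change equally and cancels between arms. On the raw pg/ml scale, at 5% per year, the difference in change retains −0.2% of baseline if the marker is flat and −2.3% if it rises 30% during pregnancy.

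**Which contrast is used.** If treatment does nothing and loss is constant and proportional, a valid 0.05-level interaction test on log concentrations is non-significant about 95% of the time. The stated rule then moves to the group main effect, which carries the full level shift δ.

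**The case against.** The strongest reply has three parts, and each has force.

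First, nothing in the documents says that any of these markers degrades at −80°C. The loss could be zero, and one rate need not fit ten analytes. This stands: the bias is conditional, and the rates above are only a range.

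Second, the plan already analyses change and a group-time interaction, in which constant proportional loss largely cancels. This also stands, and it confines the problem to comparisons of level. It does not protect the group main effect, which the plan tests precisely when the interaction shows nothing.

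Third, the single batch is sound practice. Assaying each arm in its own period would replace a storage difference with an assay-batch difference, equally tied to arm. The root cause is the sequential recruitment.

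A reader might go further and infer that plates will be filled in collection order and so split by arm. The article gives no plate layout, and a condensed article may leave that to a laboratory manual, so this is not a fault of the plan. Nor does the pg/ml sentence fix the analysis scale; it describes assay output. A reader might also infer that every intervention sample is older than every control sample, or that loss would always favour treatment. The first fails across visits, and the second fails for IL-10 and adiponectin.

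**Conclusion.** The concern holds in a limited, conditional form. The 18-month storage gap at each visit follows from the stated schedule, and neither the single batch nor the listed covariates remove it. Whether it biases anything depends on a loss rate that the documents do not give: 0–10% per year corresponds to intervention levels 0–15% lower. Between-arm differences in level, including the group main effect reached when the interaction is dropped, could then be mistaken for a treatment effect. The size also rests on the assumed log-scale SD, uniform enrolment and consecutive recruitment periods.

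It would be tempting to conclude that the trial's inflammatory results are unsound as a whole. The documents do not support that. CRP and HbA1c are measured on the day of sampling, gestational length and birth weight do not depend on stored plasma, and the group-time term is largely protected. The rule for falling back to main effects is what needs changing.

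**What to change.** For the ten stored markers, define the treatment effect as the between-arm difference in within-woman change from baseline in log concentration, that is, the group-time term. State that when this term is not significant, neither the group main effect nor an absolute pg/ml difference between arms will be read as a treatment effect.

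Keep the single batch. Place all of a woman's samples on one plate and balance the arms across plates. Record storage time for each sample.

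Baseline blood is already planned for all 1,200 recruited women, about half of whom are expected not to have periodontitis. If such women are screened in both periods, use their baseline samples to describe drift, and report it beside the arm comparison. It would show storage and calendar effects combined, not storage alone.

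No new samples are needed. The cost is some extra sorting before assay, a little more analysis, and the loss of the main-effect test for these markers.

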### Analyses of blood samples

Blood will be drawn by venipuncture into 2 ml EDTA tubes. The blood will be mixed by inversion and centrifuged at 900g in 15 min. The supernatant will be isolated, aliquoted, and stored at −80°C until analysis. Plasma levels of the proinflammatory cytokine IL-1β, IL-6, IL-10, IL-17α, TNF-α will be measured in duplicate by operators and blinded to the clinical state of the participant using Meso Scale Discovery (MSD; Rockville, MD) according to the manufacturer’s instruction. S-Plex, cat# 151B3S-1 (IL-6), cat# 151C3S-1 (IL-17α), cat# K151E3S-1 (TNF-α) and cat# K151Y2S-1 (IL-10). Analysis will be conducted on the MSD QuickPlex SQ 120 with software and the biomarker absolute values reported as absolute concentrations in picogram per milliliter (pg/ml).

### Power calculation

Statistical power was evaluated prior to commencement of the study using a two-sample means test. Minimal detectible effects for key study outcomes; gestational length (days) and birth weight (g) at 80% power and a significance level at 0.05, assuming 600 (number of enrolled) or 400 participants (200 participants with dropout and/or missing information), are presented below (Table 1).

**Table 1 pone.0302010.t001:** Power calculation.

Outcomes	Expected mean (SD)	Minimal detectable effect (n = 600)	Minimal detectable effect (n = 400)
Gestational length (days)	272 (9)	2.1	2.5
Birth Weight (g)	3490 (567)	130	159

### Statistics

Baseline characteristics of participants will be summarized using descriptive statistics (i.e. means and standard deviations for normally distributed continuous variables, medians and ranges for skewed continuous variables, frequencies and proportions for categorical/binary variables), for both treatment arms and for the total sample. All analyses will be conducted according to the intention-to-treat approach, including all participants, regardless of adherence to the study protocol. The effect of the periodontal treatment performed during pregnancy will be analyzed with regression analyses adjusted for relevant confounders (age, BMI, parity, smoking status, medicine use, socioeconomic status and education level). In addition, statistical analyses (multiple regression analysis, potentially spline analysis) of the changes in hormonal and inflammatory markers in both treatment arms will be performed. To determine the effects of the intervention, time and group-time interaction on outcomes (inflammatory and hormonal markers, glycemic control and periodontitis status), one-way repeated measures ANOVA will be applied. Procedure for testing an interaction effect: If the interaction effect is significant, provide an interpretation of the results, but do not test main effects because the tests for main effects are uninteresting in light of significant interactions. If interaction effects are non-significant, drop the interaction effects from the model and test the main effects. Determining which results to present when testing interactions is often a multi-step process. Statistical software (SPSS, (version 19, Chicago IBM) will be used. A P-value < 0.05 will be considered statistically significant.

All data will be stored in password-controlled databases, and all data will be encrypted. All data collected will be anonymized using a unique study ID. Any identifiable data (e.g. consent forms) will be stored in secure, locked facilities with access limited to the study team.

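### The fixed covariate list for this non-randomised, sequentially recruited comparison omits baseline periodontal stage, which is known for every included woman and plausibly prognostic

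*Protocol article*

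**What the plan says.** The abstract states the design: "The PROBE study is a non-randomized controlled intervention study conducted among 600 pregnant women with periodontitis". The Design section shows how the arms arise. Recruitment "will last over a period of 18 months for the intervention group and an additional 18 months for the control group", so a woman's arm follows from when she is recruited.

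The Statistics section says the effect of treatment during pregnancy will be analysed with regressions "adjusted for relevant confounders (age, BMI, parity, smoking status, medicine use, socioeconomic status and education level". These are seven named covariates. None is a periodontal measure and none is hospital, and no other section adds either to the treatment-effect model.

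Both variables are known at entry because they decide eligibility. The Design section admits women who "are diagnosed with periodontitis (stage I-III) by the study dentist" and who "are scheduled to give birth and either Holbaek Hospital or Nykoebing Falster Hospital". Under Periodontal measures, the stages are graded by severity: "Periodontitis will further be classified into stages as per the severity of the disease, defined by the worst affected tooth". The enrolled range runs from attachment loss of 1–2 mm (stage I) to 5 mm or more (stage III).

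**The concern.** Without randomisation, the covariate list is the main protection against differences between the arms. Three features of the design leave room for a different stage mix:

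- The arms are recruited in different periods.
- Only about half of the invited women are expected to accept.
- The two periods carry different offers, treatment during pregnancy or treatment after birth, which may attract different women.

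The study rests on the idea that periodontitis worsens pregnancy outcomes and that treating it may improve them. If so, women who enter with milder disease could plausibly do better whichever arm they are in. A stage imbalance could then imitate or hide a treatment effect on the two primary outcomes, gestational length and birth weight. The listed covariates (smoking, education and so on) are at best partial proxies for severity.

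**Working it through.** **Inputs from the article (Power calculation, Table 1; Design).** SD 9 days for gestational length and 567 g for birth weight; 80% power; significance level 0.05 (two-sided assumed); 300 women per arm, or 200 per arm after losses.

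**Step 1: reproduce Table 1.** Minimal detectable effect = (1.960 + 0.842) × SE, with SE = SD × √(2 / n per arm).

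- Gestational length, n = 600: SE = 9 × √(2/300) = 0.735 days; 2.802 × 0.735 = 2.06 days (stated 2.1).
- Gestational length, n = 400: SE = 9 × √(2/200) = 0.900 days; 2.802 × 0.900 = 2.52 days (stated 2.5).
- Birth weight, n = 600: SE = 567 × √(2/300) = 46.3 g; 2.802 × 46.3 = 129.7 g (stated 130).
- Birth weight, n = 400: SE = 567 × √(2/200) = 56.7 g; 2.802 × 56.7 = 158.9 g (stated 159).

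Table 1 is sound. It is an unadjusted calculation and says nothing for or against the covariate list.

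**Step 2: is stage available in both arms?** The sentence on the clinical measurements reads "will be measured at baseline (gestational week 11–20), and at gestational week 35–36 in the intervention group", and its last words could be taken to limit baseline measurement to one arm. Two other statements in the Design section rule that out: a diagnosis of stage I to III is required for inclusion, and data collection is described as the same in both groups apart from the timing of treatment. Staging itself uses attachment loss, pocket depth and missing teeth, so these must be recorded at baseline for controls too.

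**Step 3: illustrative bias.** The article reports neither the stage mix by arm nor an outcome difference between stages, so both are assumptions here. A further assumption is that the seven listed covariates absorb none of the imbalance.

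Bias = (difference between arms in the share with more severe stage) × (outcome difference for that stage).

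False-positive rate when treatment has no effect = P(|Z + bias/SE| > 1.96).

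| Outcome, n = 600 | Imbalance × difference | Bias | Bias/SE | Share of detectable effect | False-positive rate |
|---|---|---|---|---|---|
| Gestational length | 0.05 × 1 day | 0.05 day | 0.07 | 2% | 5.1% |
| Gestational length | 0.05 × 2 days | 0.1 day | 0.14 | 5% | 5.2% |
| Gestational length | 0.10 × 4 days | 0.4 day | 0.54 | 19% | 8.5% |
| Gestational length | 0.15 × 4 days | 0.6 day | 0.82 | 29% | about 13% |
| Gestational length | 0.20 × 4 days | 0.8 day | 1.09 | 39% | 19.3% |
| Birth weight | 0.05 × 50 g | 2.5 g | 0.05 | 2% | 5.0% |
| Birth weight | 0.20 × 200 g | 40 g | 0.86 | 31% | 13.9% |

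For the 0.6-day row: 0.6/0.735 = 0.82, and P(Z > 1.14) + P(Z < −2.78) ≈ 0.127 + 0.003 = 0.13.

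**Step 4: cost of adjusting.** Stage as a three-level factor takes 2 degrees of freedom and hospital takes 1, so 3 in total. If the added covariates explained an assumed 0% to 10% of the variance, the detectable effect at n = 600 would go from 2.06 to 1.95 days (2.06 × √0.90 = 1.95) and from 129.7 to 123.0 g, ignoring any correlation of the covariates with arm. No larger sample is needed.

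**The case against.** Several points can fairly be put against this.

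- **The study does not name severity as a cause.** A reader might infer that the study's own hypothesis makes stage a cause of early birth. The Abstract, Introduction and statement of aims link the presence of periodontitis, and its treatment, to outcomes. They state no gradient across stages I to III, and every enrolled woman has the disease. That stage is prognostic is a plausible inference from the treatment rationale, and no more. This objection stands.
- **The bias need not pass through in full.** A reader might infer that any imbalance goes straight into the estimate. Age, BMI, smoking, socioeconomic status and education could carry part of a severity difference. This stands, and the figures above are therefore conditional on no absorption.
- **Adjustment cannot cure drift in grading.** One study dentist performs all examinations over the two periods. If the grading shifted over time, recorded stage would mean different things in the two arms, and adjusting for it could even add bias. Whether the examiner is blinded is not stated and should not be assumed either way. This limits the remedy to true differences in case mix.
- **Hospital is the weaker omission.** The Design section says "approximately 1200 pregnant women are recruited from Holbaek Hospital and Nykoebing Falster Hospital", with no staggering by site. Hospital confounds only if its share differs between the periods, which the article does not suggest.
- **A fuller analysis plan might extend the list.** That is possible, but the article presents the covariates as settled.

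None of this removes the central fact: a variable that defines the treated condition, and is recorded for everyone, is absent from the adjustment set of a non-randomised comparison.

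**Conclusion.** The point holds in a limited form. The adjustment set omits baseline periodontal stage, and a true difference in stage mix between the arms could bias the primary estimates as far as the listed covariates fail to absorb it.

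The omission is certain from the text; the consequence is not. Under assumed inputs it ranges from negligible (0.1 day or less) to material (0.6 to 0.8 day, against a detectable effect of 2.1 days). The upper end needs a 4-day difference between enrolled stages, almost twice the detectable effect, together with an imbalance of 15 to 20 points. The article does not show that any such bias will occur, nor that adjustment would remove all of it. The change is worth making because it is nearly free. It does not touch the larger limitation that arm coincides with recruitment period.

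**What to change.** In the Statistics section:

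1. Add baseline periodontal stage (I, II, III) to the pre-specified covariates of the models for gestational length and birth weight. One continuous severity measure, such as baseline attachment loss, would serve instead. Stage is itself defined largely by attachment loss, so several overlapping measures should not be entered together.
2. Add hospital as a secondary covariate.
3. Name both variables in the baseline table by arm. The section already plans baseline summaries for each arm but does not name these two.
4. State that this adjustment addresses true case-mix differences only, that it does not correct a change in the examiner's grading over time, and that calendar period remains confounded with arm.

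The cost is 3 degrees of freedom for stage plus hospital (2 with a single continuous severity measure) among 400 to 600 women, with no new data and no increase in sample size. The change should be fixed before outcomes are analysed.

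### The one-way repeated measures ANOVA named for the marker and periodontal outcomes has no group term, so it cannot give the intervention or group-by-time effect assigned to it

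*Protocol article*

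**What the plan says.** The Statistics section of the protocol article states the aim of the repeated-measures analysis: "To determine the effects of the intervention, time and group-time interaction on outcomes". The outcomes and method follow: "inflammatory and hormonal markers, glycemic control and periodontitis status), one-way repeated measures ANOVA will be applied". The section then gives a testing sequence in which a significant interaction is interpreted alone; otherwise, "If interaction effects are non-significant, drop the interaction effects from the model and test the main effects".

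The same section sets the analysis population: "All analyses will be conducted according to the intention-to-treat approach, including all participants, regardless of adherence to the study protocol". It plans regression adjusted for age, BMI, parity, smoking, medicine use, socioeconomic status and education for the effect of treatment, and a separate regression (possibly with splines) of changes in hormonal and inflammatory markers.

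Under Blood samples, all recruited women are sampled at baseline (weeks 11–13), with further samples "in gestational week 20–22 and at gestational week 35–37 from the included women (n = 600"). Under Periodontal measures, the examination is done at baseline "and at gestational week 35–36 in the intervention group". The Design section says that data collection does not differ between the groups apart from the timing of treatment.

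**The concern.** The method and its task do not match. In a one-way repeated measures ANOVA the only factor is time. It tests whether the mean marker level changes over pregnancy in the pooled women, not whether treated and untreated women differ or change differently. Changes in systemic inflammation are the second of the study's two stated aims, so this sentence governs a main result. Followed literally, it could lead to the ordinary course of a marker over pregnancy being reported as if it bore on treatment.

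Reading the sentence as a mislabelled two-factor ANOVA leaves two weaknesses. The classical procedure needs a value at every visit, so a woman with one missing sample also loses her other values. And the sentence names no covariates, although the abstract calls the study non-randomized and the Design section gives the controls a further 18 months of recruitment in addition to the 18 months for the intervention group. Group differences in season, calendar time or case mix would go straight into an unadjusted contrast.

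**Working it through.** **1. Terms in the two models.** Inputs: N = 600 women, 300 per arm (Design); k = 3 blood samples (Blood samples); all visits complete.

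- One-way: time, k − 1 = 2 df; women, N − 1 = 599 df; error, (N − 1)(k − 1) = 599 × 2 = 1198 df. Total 1799.
- Group by time: group, 1 df; women within group, N − 2 = 598 df; time, 2 df; group-by-time, 2 df; error, (N − 2)(k − 1) = 598 × 2 = 1196 df. Total 1799.

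In the one-way model the group effect is buried in the 599 df between women (1 + 598), and the interaction is buried in the error (2 + 1196). Neither is estimated or tested. The instruction to drop a non-significant interaction has nothing to act on.

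**2. What the one-way test responds to.** Simulation with 400 replicates, 300 women per arm and 3 visits. Assumptions, not from the protocol: within-woman correlation 0.6; a time trend reaching 0.4 SD at the last visit; a treatment effect at the last visit of either 0 or −0.3 SD, with half of that at the middle visit.

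| Test | No treatment effect | Effect −0.3 SD |
|---|---|---|
| One-way, time | rejects in 100% | rejects in 100% |
| Two-factor, group-by-time | rejects in 4.5% | rejects in 98.8% |

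The one-way test gives the same answer whether or not treatment works.

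**3. What the 200 of 600 refers to.** The Power calculation section gives detectable effects for 600 women or for "400 participants (200 participants with dropout and/or missing information"). With 80% power and 0.05 (taken as two-sided), the effect is (1.960 + 0.842) × SD × √(2/n per arm):

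- Gestational length, SD 9 days: 2.06 days with 300 per arm, 2.52 with 200 (Table 1: 2.1 and 2.5).
- Birth weight, SD 567 g: 129.7 g and 158.9 g (Table 1: 130 and 159).

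The table reproduces. The 400 is the sample size of a second power scenario for these two outcomes. It says nothing about how many women lack a blood sample.

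**4. Women who cannot give the last sample.** From Table 1, gestational length has mean 272 and SD 9 days. Assuming normality:

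- Before 35w0d (245 days): Φ((245 − 272)/9) = Φ(−3) = 0.0013; × 600 = 0.8, about 1 woman.
- Before 37w0d (259 days): Φ((259 − 272)/9) = Φ(−1.44) = 0.074; × 600 = 44.6, about 45 women. The sampling window opens at week 35, so many of these could already have been sampled. This is not a count of missing samples.

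Gestational length usually has a longer left tail than the normal. If 1% to 3% delivered before 35 weeks (an assumption; the document gives no figure), that would be 6 to 18 women.

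**5. Periodontal status.** The Periodontal measures section names the week 35–36 examination for the intervention group. The Design section says both groups have the same data collection. If the first is literal, controls have only a baseline value, and no model can give a group-by-time effect for periodontal status. The schedule figure (Fig 1) may settle this but could not be read in the text at hand.

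**The case against.** The best defence is that this is a naming slip. The sentence lists the effects wanted, and the following lines describe a two-factor analysis, so the authors probably meant a mixed ANOVA and the label could simply be corrected. That is likely true of the intention, but the method as written is still wrong, and the relabelled method still has the visit-completeness and adjustment problems.

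Second, no section says that incomplete cases are dropped. Deletion is inferred from how classical repeated measures ANOVA works, and an analysis plan not shown could add imputation. The intention-to-treat sentence can also be read as being about adherence rather than missing samples. This stands: the conflict with including everyone is a tension that depends on the procedure used, not a stated contradiction.

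Third, a reader might infer that a third of the women would be deleted, or that early delivery would remove a sizeable group. The document supports neither: the 200 belongs to a power scenario for other outcomes, and the plan's own figures put delivery before 35 weeks at about 1 in 600.

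Fourth, the adjusted-regression sentence names no outcome and might be meant to cover the markers too, and a regression of marker changes is planned separately. That softens the concern for the hormonal and inflammatory markers. It does not tell the analyst to adjust the ANOVA, and the change regression is not stated to cover glycaemia or periodontal status.

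Finally, a mixed model does not fully resolve absence due to delivery. This is correct, and the fix below says so.

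**Conclusion.** The point holds for the named model: a one-way repeated measures ANOVA cannot give the group or group-by-time effect, and it contradicts the interaction procedure in the same paragraph. That rests on the text and on the definition of the method. The completeness requirement is conditional on a classical two-factor ANOVA being used in its place. The absence of adjustment rests on the wording of that sentence in a non-randomized design.

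The size of the missing-data problem is not known from the document. Early delivery matters because it is tied to gestational length, a primary outcome, but on the normal assumption it concerns very few women.

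A reader might infer that the main trial results are compromised. They are not: gestational length and birth weight are single measurements outside this sentence's outcome list, and adjusted regression is planned for the treatment effect. This should be fixed before analysis because it governs a stated aim, but it does not threaten the primary comparison.

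**What to change.** In the Statistics section, replace the ANOVA sentence with a linear mixed model for the repeated outcomes, fitted to all available measurements. Fixed effects: arm, visit, arm-by-visit and the confounders already listed in that section; repeated measures correlated within woman. For the blood markers, report the arm-by-visit contrasts at weeks 20–22 and weeks 35–37. Revise the interaction procedure to match.

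Report per arm how many women delivered before the week 35–37 sample. The mixed model keeps their earlier samples but assumes that values are missing at random, and a marker level in late pregnancy is not well defined for a woman who has already delivered. The count shows the reader how much rests on that.

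Reconcile the Periodontal measures and Design sections on whether controls have the week 35–36 examination. Until that is settled, no group-by-time effect on periodontal status should be promised.

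The cost is wording only. The sample size and Table 1 do not change, and the SPSS software already named has a mixed-model procedure.
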